## Abstract

**Introduction:** Non-melanoma skin cancer (NMSC) incidence is increasing, and occupational solar exposure contributes greatly to the overall lifetime ultraviolet radiation (UVR) dose. This is reflected in an excess risk of NMSC showing up to three-fold increase in outdoor workers. Risk of NMSC can be reduced if appropriate measures to reduce UVR-exposure are taken. Regular use of sunscreens showed reduced risk of NMSC. However, sun-safety behavior in outdoor workers is poor. The objective of this study is to investigate the effectiveness of an intervention aiming at increasing sunscreen use by construction workers.

**Methods:** This non-randomized controlled intervention study is comprised of two intervention and two control groups recruited at four different construction sites in the Netherlands. The study population comprises ~200 construction workers, aged 18 years or older, followed during 12 weeks. The intervention consists of providing dispensers with sunscreens (SPF 50+) at construction sites and regular feedback on the application achieved by continuous electronic monitoring. All groups will receive basic information on UV-exposure and skin protection. Stratum corneum (SC) samples will be collected for measurement of biomarkers to assess internal UV-dose. External UV-dose will be assessed by personal UV-sensors worn by the workers during work-shifts in both groups. To detect presence of actinic keratosis (AK) or NMSC, a skin check of body parts exposed to the sun will be performed at the end of the study. The effect of the intervention will be assessed from data on self-reported sunscreen use by means of questionnaires collected on baseline and after 12 weeks of intervention (primary outcome). Levels of SC biomarkers of internal UV-dose, external UV-dose, number of sunburn episodes, and prevalence of NMSC including AK will be assessed as secondary outcomes. The electronically monitored sunscreen consumption will be assessed as process outcome.

**Discussion:** This study is intended to provide evidence of the effectiveness of a technology-driven intervention to increase sunscreen use in outdoor construction workers. Furthermore, it will increase insight in the UV-protective behavior, external and internal UV-exposure, and the prevalence of NMSC, including AK, in construction workers.

**Trial Registration:** The Netherlands Trial Register (NTR): NL8462 Registered on March 19, 2020.

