## Methods/Design

### Design and Setting

This is a non-randomized controlled intervention study in construction workers. The duration is 12 weeks, from May to July. The measurements will consist of questionnaires, clinical and biochemical assessments, personal UV-dosimetry, and continuous electronic sunscreen consumption records. When reporting the results of this study we will adhere to the Transparent Reporting of Evaluations with Non-randomized Designs (TREND) statement (24).

A nationwide construction company in the Netherlands will appoint four comparable construction sites suitable for the study. Two sites will serve as the intervention groups and the other two construction sites will serve as the control groups. To minimize potential bias induced by non-randomization, the control groups will be matched to the intervention groups regarding worksites and job tasks, geographical location of the worksites, and time-frame. To avoid contamination bias, the whole construction site will be assigned en masse to the intervention group and there will be no rotation of workers between the four workplaces.

A process evaluation of the intervention will take place in the closing questionnaire to support a future implementation process.

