**Figure 1 F1:**
[figure not shown]
Flowchart of the study design.

The researchers will visit the worksites of the intervention and control groups three times (at T = 0, T = 6 weeks, and T = 12 weeks). The participants will be asked to fill in a questionnaire at the start (T = 0) and the end of the study (T = 12 weeks). At T = 0, T = 6 weeks, and T = 12 weeks, stratum corneum (SC) samples will be collected, and measurements of personal UV-exposure by using personal dosimeters will be performed during work shifts for 1 week (Monday to Friday). At the end of the study (T = 12 weeks), the participants will undergo a skin check of the sun-exposed body parts for the presence of AK and NMSC by a trained investigator (physician). The intervention and control groups will receive basic information (i.e., a 15-min Powerpoint presentation) on the nature of the study and sun-safety and UV-protective behavior at the beginning of the study (baseline).

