#### Skin Check

At the end of the study (T = 12 weeks), a skin check of the sun-exposed skin by a trained investigator (physician) will be performed on the participants of all groups. Besides examination for NMSC and AK, following clinical features (42), skin photo type following Fitzpatrick (43) will be recorded. Furthermore, skin photo damage will be assessed by the validated Glogau photo damage classification scale (44).

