### Statistical Methods and Data Analysis

There will be no replacement of any individual subjects who withdraw. However, the characteristics (e.g., job task, age) and number of withdrawals will be monitored.

The characteristics of the construction workers (e.g., age) and job tasks will be presented by using descriptive statistics. We will use the mean and standard deviation to describe normally distributed continuous variables and the median and interquartile range to describe non-normally distributed continuous variables. For the self-reported sunscreen usage data (primary outcome), counts and percentages to present categorical variables will be used. The self-reported sunscreen usage data will be dichotomized and analyzed by Chi-squared statistical test to establish whether sunscreen consumption will differ between the intervention and control groups. Two-sided *p*-values of <0.05 will be considered statistically significant and statistical uncertainty will be expressed using two-sided 95% confidence intervals. For the main study parameter, intention-to-treat analysis will be performed.

For the secondary study parameters we will present the levels of biomarkers and the number of sunburn episodes as quantitative, continuous variables. The biomarker levels at T = 6 weeks and T = 12 weeks will be compared with the baseline levels using paired ANOVA test followed by the correction for multiple testing, dependently on the distribution of data. The presence of NMSC including AK will be presented as counts and percentages.

UV-exposure measured by UV-dosimeters will be presented per job task, and as average of the measurements by all workers who worn the dosimeter in the same period. Data will be presented as average dose per day. Furthermore, the UV-exposure pattern during the work shift will be revealed.

The distribution will be tested by using Shapiro-Wilk normality test.

Before data analysis, a detailed data analysis plan will be available.

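### The primary chi-squared comparison of two against two non-randomised sites gives the collected baseline sunscreen answer no role

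*Protocol article*

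**What the plan says.** **Design.** Design and Setting states: "This is a non-randomized controlled intervention study in construction workers". Allocation is by site, since "the whole construction site will be assigned en masse to the intervention group", with two sites in each arm. The stated safeguard is that "the control groups will be matched to the intervention groups regarding worksites and job tasks, geographical location of the worksites, and time-frame". The Discussion repeats the matching (adding equal sample size) and acknowledges the lack of randomisation as a limitation.

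**Data collected.** Under Description of the Study Procedures and Intervention: "The participants will be asked to fill in a questionnaire at the start (T = 0) and the end of the study (T = 12 weeks"). The Questionnaires section lists sunscreen use among the items.

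**Role of the data.** Four places bear on how the two answers are to be used:

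- The Abstract bases the effect on "self-reported sunscreen use by means of questionnaires collected on baseline and after 12 weeks of intervention (primary outcome").
- Primary Outcome defines a between-group difference in frequency of use on a five-level scale. It names no time point, change score or baseline term.
- Power Calculation says that the sample size rests on an expected change in use, but the calculation itself compares two independent proportions, 25% and 50%.
- Statistical Methods and Data Analysis dichotomises the answer, which is then "analyzed by Chi-squared statistical test to establish whether sunscreen consumption will differ between the intervention and control groups". No covariate is named. The same section compares the biomarkers, a secondary outcome, with their own baseline.

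**The concern.** In a randomised trial, leaving out the baseline value would mainly cost precision. Here two sites are compared with two others that were not chosen at random, so sites that already differ in sunscreen habit produce a systematic error. A between-group test of week-12 use cannot separate that difference from the effect of dispensers and feedback. If the intervention sites start higher, the effect is overstated; if the control sites start higher, it is understated.

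Matching on worksite, job task, location and period should bring the sites closer together. It does not include prior sunscreen use, which is the outcome's own starting value. The Introduction itself names beliefs about tanned or dark skin and attitudes to tanning as influences on use, and the matching list does not include these either. The T = 0 answer that would show and partly correct such a difference is already being collected.

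**Working it through.** **Inputs from the Power Calculation section:** 25% users in the control arm, 50% in the intervention arm, two-sided test, significance level 0.05, power 80%, 58 per arm, 100 per arm recruited. **Assumed, because the documents give no figure:** the size of the pre-existing gap, its full persistence to week 12, and the within-worker correlation used in step 3.

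**1. The plan's own figure.** With pooled variance and no continuity correction,

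n = [1.960·√(2p̄(1−p̄)) + 0.842·√(p₁(1−p₁)+p₂(1−p₂))]² / (p₂−p₁)².

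With p₁ = 0.25, p₂ = 0.50 and p̄ = 0.375, this is [1.960·√0.46875 + 0.842·√0.4375]² / 0.0625 = (1.342 + 0.557)² / 0.0625 ≈ 57.7, so 58 per arm. Power is 80.2% at 58 per arm and 96.0% at 100. The sample-size figure is not in dispute.

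**2. Rejection rate with no intervention effect and a persisting gap.** Let d = p₂−p₁, SE₀ = √(2p̄(1−p̄)/n) and SE₁ = √((p₁(1−p₁)+p₂(1−p₂))/n). The two-sided rejection rate is

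Φ((d − 1.96·SE₀)/SE₁) + Φ((−d − 1.96·SE₀)/SE₁).

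Example, 25% against 35% at n = 100: SE₀ = √(0.42/100) = 0.0648 and SE₁ = √(0.415/100) = 0.0644. The first term is Φ((0.10 − 0.127)/0.0644) = Φ(−0.42) ≈ 0.338; the second is negligible.

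| Control vs intervention sites | 58 per arm | 100 per arm |
|---|---|---|
| 25% vs 25% | 5.0% | 5.0% |
| 25% vs 30% | 9.2% | 12.4% |
| 25% vs 35% | 21.6% | 33.8% |
| 25% vs 40% | 40.6% | 62.1% |

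The rates rise with sample size because the error is bias, not sampling noise.

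**3. What using the baseline answer changes.** In a simulation of 4,000 runs per setting, with no intervention effect, gaps of 25% vs 35% or 40%, and a within-worker correlation of 0.5 or 0.7 between the two binary answers:

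| Analysis | Rejection rate over the settings |
|---|---|
| Unadjusted chi-squared | 22% to 63% |
| Mantel-Haenszel, stratified by dichotomised baseline | 8% to 26% |
| Change score (difference-in-differences) | about 5% to 6% |

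Conditioning on a single yes/no baseline answer therefore removes much of the excess but not all of it. The change-score result is favourable partly by construction: in the simulation each arm's proportion stays constant over time, which is the parallel-trends condition that difference-in-differences needs. Adjustment for the full five-level answer was not simulated, and no calculation here includes clustering by site.

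**The case against.** **The time point.** The analysis section does not say that only the week-12 answer is tested, and a chi-squared test could be run on a dichotomised change. A reader might take the week-12-only analysis as stated. It is an inference: the outcome definition and the two-proportion sample size fit it, while the Abstract and the reference to change in the Power Calculation point the other way. This objection stands, and the rates in step 2 apply only under the week-12 reading. What is certain is that the sections do not say how baseline enters.

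**The promised analysis plan.** The protocol announces a detailed data analysis plan before analysis, and covariate lists usually belong there. That is a good answer to a complaint about missing detail. It does not dispose of the point, because the protocol already names an unadjusted test as its primary analysis.

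**Size and persistence.** All arms receive sun-safety information at baseline, which the Discussion says may change behaviour in the control groups. The question covers the preceding month and the study runs from May to July, so the T = 0 answer describes roughly April. Full persistence of a gap is therefore an assumption, and a 5-point gap does much less harm than a 15-point one.

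**Stronger readings that the documents do not support.**

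- That every pre-existing difference will appear as an effect. The stated aim, "To minimize potential bias induced by non-randomization, the control groups will be matched to the intervention groups", covers features that should limit some differences.
- That baseline adjustment brings a fixed gain in precision of 1−ρ². That is a linear-model result. It does not carry over to an odds ratio, and an individual-level correlation does not describe precision when four whole sites are assigned.
- That the timing of skin type is a defect because "skin photo type following Fitzpatrick (43) will be recorded" at the closing skin check. Workers who leave before week 12 also lack the week-12 outcome, so an earlier recording would add little to the primary comparison.

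**Conclusion.** The point holds. The protocol fixes an unadjusted between-group test as the primary analysis of a non-randomised comparison of two against two sites, and gives the T = 0 answer no role although the Abstract says that the effect rests on both questionnaires. Prior sunscreen use is outside the matching, so a remaining difference would be read as an intervention effect.

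How large that difference would be cannot be learned from the documents. Under the week-12 reading, with assumed gaps of 5, 10 and 15 points, full persistence and no intervention effect, the test rejects in about 9%, 22% and 41% of studies at 58 per arm, and 12%, 34% and 62% at 100 per arm, against a nominal 5%. These figures illustrate sensitivity; they are not a forecast. Confidence is high on the absent baseline term and lower on the size of its consequence.

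**What to change.** Reconcile the Abstract, Primary Outcome, Power Calculation and Statistical Methods sections by stating one primary contrast that uses the T = 0 answer. Either of these would serve:

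- a group-by-time (difference-in-differences) comparison of use at T = 0 and T = 12 weeks; or
- a regression of week-12 use on group and the worker's T = 0 answer, entered on its full five levels rather than dichotomised.

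Add only a few prespecified confounders, such as age and job task. Under the planning assumptions there are about 0.25×58 + 0.50×58 ≈ 44 users at 58 per arm, or 75 at 100 per arm, which will not carry a long covariate list. Report the estimate with its 95% confidence interval and keep the unadjusted chi-squared test as a secondary result. State that the baseline-using analysis reduces but does not remove confounding, and that it does not deal with clustering within four sites, which needs its own treatment.

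The cost is a change of wording. The data are already collected at planned visits, no participants or procedures are added, and the Study Status section says that recruitment had not begun at submission.

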#### Collection of SC Samples: Procedure of Tape Stripping

During the study, SC samples will be collected at the beginning (T = 0), half-way (T = 6 weeks), and at the end of the study (T = 12 weeks) in both groups. The SC will be collected by using adhesive tape strips with a minimally invasive, non-painful method which is extensively used in experimental studies (28–30). Adhesive tape discs (3.8 cm^2^, D-Squame; CuDerm, Dallas, TX, USA) will be attached to the skin. Each tape is pressed on the skin for 5 sec with standardized force, using a disc pressure applicator (CuDerm). The tape strips will be removed gently with tweezers and stored in a closed vial at −80°C until analysis. The samples will be taken from skin sites exposed to the sun (i.e., forehead), and a less-exposed skin site (i.e., behind the ear).

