#### Analysis of the Markers of the Internal UV-Dose

The markers of the internal UV-dose will include the *cis-* and *trans-*isomers of urocanic acid (UCA), and immune markers of different signature such as matrix metalloproteinases (MMP), cytokines, and angiogenesis factors. The isomers of UCA are one of the most studied UVR-related biomarkers (31–34). *Trans*-urocanic acid (tUCA) is a major UVR-absorbing component in the epidermis and it isomerizes to the *cis-*form (cUCA) upon exposure to UVB in a dose-dependent manner until reaching a photo stationary state at ~60–70% of total UCA (35). That makes cUCA a very specific marker as it is not endogenously present but is formed upon exposure to UVR (36). Immunological markers have been proposed to assess the effects of UVR-exposure (37–40), as the adverse effects of UVR might have occurred before visible changes occur (erythema of the skin), and furthermore, immune response in the skin plays an important role in UVR-mediated damage (41). Immunological markers might be in particular useful to assess repeated exposure to UVR (29).

The markers will be extracted from the tape using a buffer, and subsequently analyzed using an appropriate technique. For urocanic acid, HPLC (High Performance Liquid Chromatography) method will be used, and for cytokines the multiplex immuno-assay (MSD–Meso Scale Discovery LLC, Maryland, U.S.A.). For all analyses, standard operating procedures (SOP) will be used. The analysis of the markers will be performed blinded, the samples will be coded untraceable to the participants (the codes will be open after data analysis has been performed).

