#### Secondary Outcomes

Several secondary outcomes will be assessed:

Internal UV-dose will be determined by measuring the SC levels of UCA isomers and immunological markers measured in the intervention and control groups at T = 0, T = 6 weeks, and T = 12 weeks.Levels of external UV-exposure in construction workers, measured using Scienterra UV-dosimeters at T = 0, T = 6 weeks, T = 12 weeks.The prevalence of NMSC including AK in construction workers as assessed at T = 12 weeks by a skin check.The number of reported episodes of sunburn during the study period as obtained from the closing questionnaire at T = 12 weeks.

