## Discussion

The overall purpose of this study is to evaluate the effectiveness of an intervention comprising the facilitation of sunscreen dispensers and regular feedback on sunscreen use in outdoor construction workers. Next, this study will provide insight in UV-exposure, and prevalence of NMSC including AK in construction workers in the Netherlands.

The effectiveness of the intervention will be assessed from self-reported data on sunscreen use (primary outcome), and the changes in the levels of biomarkers of internal UV-dose measured at baseline and after 6 and 12 weeks (secondary outcome). To evaluate the process of the intervention, electronically monitored sunscreen consumption will be used. Furthermore, satisfaction regarding intervention and main barriers for using of sunscreens will be investigated in construction workers.

The intervention is easy and straightforward, and as such the expectation is, that it should be feasible to implement on construction sites. The results of this study will gain insight into the effectiveness of the intervention on UV-protection, and will provide relevant data on the use of sunscreen in outdoor work situations and on the occupational UV-exposure of construction workers.

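### The only biomarker test stated compares each follow-up with baseline and has no between-arm contrast, although biomarker change is meant to help assess effectiveness

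*Protocol article*

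**What the plan says.** In the protocol article, Statistical Methods and Data Analysis gives one inferential analysis for the biomarkers: "The biomarker levels at T = 6 weeks and T = 12 weeks will be compared with the baseline levels using paired ANOVA test". A multiplicity correction is to be applied afterwards, by a method the section does not specify. It names no arm term, no arm-by-time term and no contrast between groups for these markers. The only between-arm test in that section is the chi-squared test of dichotomised self-reported sunscreen use.

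The Discussion gives the markers a larger role. It opens the relevant sentence with "The effectiveness of the intervention will be assessed from self-reported data on sunscreen use (primary outcome" and then adds, as a second source of evidence on effectiveness, "the changes in the levels of biomarkers of internal UV-dose measured at baseline and after 6 and 12 weeks (secondary outcome".

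The data for a between-arm comparison are planned: Secondary Outcomes has the markers "measured in the intervention and control groups at T = 0, T = 6 weeks, and T = 12 weeks". On timing, Design and Setting says "The duration is 12 weeks, from May to July". On what moves the marker, the section on markers of internal UV-dose says of trans-urocanic acid that "it isomerizes to the *cis-*form (cUCA) upon exposure to UVB in a dose-dependent manner", up to a plateau at about 60–70% of total urocanic acid.

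**The concern.** The stated purpose and the stated test do not match. Effectiveness is a contrast between workers with and without the dispensers and feedback. A comparison of week 6 and week 12 with baseline answers a different question: whether levels moved over the study.

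The documents name two reasons why levels might move in both arms. The markers respond to UV exposure, and follow-up runs through late spring and summer. Both arms also receive the sun-safety presentation at baseline, and the Discussion accepts that this may change behaviour in the control groups. The control arm is there to remove such shared changes, and the stated test does not use it for that.

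This matters because participants and investigators are unblinded and the primary outcome is self-reported. The biomarkers are the effect measure available in both arms that is analysed blind in the laboratory. Sunburn is also self-reported, and dosimetry records external dose in only 10 workers per group.

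**Working it through.** **The plan's own figure.** No sample size or power is given for the biomarkers. The figure of 58 per group is for the primary outcome (25% v 50%, two-sided 0.05, 80% power). With pooled variance and no continuity correction:

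n = [1.960·√(2·0.375·0.625) + 0.842·√(0.25·0.75 + 0.50·0.50)]² / 0.25² = (1.342 + 0.557)² / 0.0625 ≈ 57.7, so 58.

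It reproduces. It does not bear on this point except to supply a realistic n. The other n used is the planned recruitment of 100 per group.

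**What each comparison estimates.** Let D be the mean change from baseline shared by both arms and δ the additional change caused by the intervention.

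- Control arm against its baseline: D
- Intervention arm against its baseline: D + δ
- Both arms pooled (equal size) against baseline: D + δ/2
- Between-arm difference in change: (D + δ) − D = δ

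The protocol does not say whether the paired test is run per arm or pooled. In neither case is δ isolated.

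**Size of the problem.** The documents give neither D nor the SD of change, so these are assumptions: D of 0.2, 0.3 or 0.5 SD of change, δ = 0, independent workers. With d = D/SD, the chance that a within-arm comparison at one time point is significant is

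P = Φ(d√n − 1.96) + Φ(−d√n − 1.96).

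| d | n = 58 | n = 100 |
|---|---|---|
| 0.2 | 33% | 52% |
| 0.3 | 63% | 85% |
| 0.5 | 97% | >99% |

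For example, d = 0.3 and n = 58 gives 0.3·7.616 = 2.285, and Φ(0.325) = 0.627.

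The correction method is not specified. If it were a split of alpha over the two follow-up times (0.025 each), the figures would be 24%, 52% and 94% at n = 58, and 41%, 78% and >99% at n = 100. Correction for multiplicity lowers the rates but does not remove the shared drift.

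**The opposite error.** Suppose the intervention fully cancels a rise of 0.5 SD (D = 0.5, δ = −0.5). The intervention arm's mean change is then zero, and its paired test is significant in 5% of trials, so a successful intervention looks like no change. Power of the between-arm test is Φ(0.5·√(n/2) − 1.96): 77% at n = 58 and 94% at n = 100. A simulation of 20,000 trials with t-tests gave 76% and 94%. With δ = 0 and drift of 0.3 or 0.5 SD, the simulated between-arm test rejected in about 5% of trials.

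All of these figures treat workers as independent. With four whole sites assigned, the between-arm power is optimistic, and an unclustered between-arm test need not hold its 5% error rate.

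**The case against.** The strongest reply is that this is a condensed article which promises a detailed analysis plan before data analysis, and that markers listed for both groups are plausibly meant to be compared between them. That stands as a limit: a reader might infer that no between-arm biomarker analysis will ever be done, or that the biomarkers cannot show effectiveness. The documents support neither. They show only that none is stated here. It does not remove the point, because the article goes beyond silence: it fixes a specific test, and that test does not serve the purpose the Discussion gives it.

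A second reply is that the seasonal drift has no documented size or direction. That also stands. If outdoor workers already have cis-urocanic acid near its plateau at baseline, drift in that marker could be small. The percentages above are therefore conditional on assumed values.

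Two further readings are tempting and should be resisted:

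- A reader might infer that significance in one arm will be set against non-significance in the other. That would be unsound: with 0.3 SD shared drift and no effect, the arms disagree in 47% of simulated trials at n = 58 and 26% at n = 100. But the plan never says it will do this, and the rate falls to 7% at n = 58 with 0.5 SD drift.
- A reader might fault the plan for not using the second sampling site, described as "and a less-exposed skin site (i.e., behind the ear". The protocol does not call it a reference site, it is less exposed and not unexposed, and its use is ordinary analysis-plan detail. It is no error.

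**Conclusion.** The point holds as a mismatch between purpose and test. The Discussion uses biomarker change to help assess effectiveness, and the one biomarker test stated does not estimate the intervention effect. Shared changes may be mistaken for an effect or may hide one. Under an assumed shared drift of 0.2 to 0.5 SD of change and no intervention effect, the within-arm baseline comparison would be significant in about 33% to 97% of trials at 58 per arm, ignoring clustering and the multiplicity correction.

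It should be fixed, but it does not threaten the main result: the biomarkers are secondary, the hypothesis concerns sunscreen use, and the primary outcome has a stated between-arm test.

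**What to change.** In Statistical Methods and Data Analysis, state that the effect of the intervention on biomarkers will be estimated by comparing the arms at weeks 6 and 12, adjusted for each worker's baseline level. A repeated-measures model with arm, time and arm-by-time would do this. Report the adjusted arm difference at each time with its 95% CI. Keep the paired comparison with baseline as description.

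Account for the four sites by a random site term or a small-sample cluster method. Fixed site effects will not work: sites are nested in arm, two per arm, so arm and fixed site effects cannot be estimated together. State also that four sites leave the estimate imprecise. Site-level inference has about 4 − 2 = 2 degrees of freedom, for which the 97.5% t quantile is 0.95/√(2·0.975·0.025) = 4.30, against 1.96 for a large sample. Because sites are not randomised, the comparison removes only changes that the arms share.

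The cost is a wider, more honest interval and slightly more analysis work. No extra sampling is needed, since both arms are already due to be sampled at all three times. Study Status says recruitment had not started at submission, so when the article was submitted the wording could still be settled before any data were seen.

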### Power Calculation

The study is planned to include 200 participants. The sample size is based on the expectation regarding the change in sunscreen usage. There is no available data on sunscreen use in outdoor workers in the Netherlands, or the barriers for sunscreen use. Therefore, we based our calculations of the sample size on a Canadian study reporting that 25% of the outdoor workers used sunscreen regularly (47). We assumed that 25% of the outdoor workers in the control groups will use sunscreen, and that in the intervention groups we expect this percentage will increase up to 50%. To calculate the sample size, nQuery Advisor software (Statistical Solutions Ltd, Boston, MA, U.S.A.) was used (proportion, two groups, two-sided test). A sample size of 58 workers per group will have 80% power to detect a difference in proportion that equals at least 0.05 significance level. Taking into account possible drop-outs, 100 outdoor workers per group will be recruited.

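### If run as a classical repeated-measures ANOVA, the biomarker analysis would use only workers with all three samples and leave out week-6 samples of workers who later withdraw

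*Protocol article*

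**What the plan says.** The tape-stripping section sets three sampling times in both arms: "SC samples will be collected at the beginning (T = 0), half-way (T = 6 weeks), and at the end of the study". The Statistical Methods and Data Analysis section then fixes the test: "The biomarker levels at T = 6 weeks and T = 12 weeks will be compared with the baseline levels using paired ANOVA test". The rest of that sentence adds a multiplicity correction and makes the approach depend on how the data turn out to be distributed.

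The same section says of withdrawals: "There will be no replacement of any individual subjects who withdraw". It adds that their number and characteristics will be monitored. Intention-to-treat is given a limited scope: "For the main study parameter, intention-to-treat analysis will be performed". For biomarkers the article defines no completer set, no exclusion rule and no rule for missing samples. The section closes with: "Before data analysis, a detailed data analysis plan will be available".

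The Power Calculation requires 58 workers per arm and recruits 100 to allow for drop-outs. It states no dropout rate.

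**The concern.** The article names a method here, so this is not only a matter of detail left to a later document. An ANOVA on three paired measurements, followed by multiplicity correction, usually means a repeated-measures ANOVA with post-hoc comparisons. In its classical form it works on complete triplets. The usual rank-based substitute for skewed data, the Friedman test, does so too, so the clause on the distribution of the data does not remove the problem.

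Two kinds of worker would be affected. One gives samples at baseline and week 6 and then leaves; the week-6 sample has been taken and assayed but does not enter the week-6 comparison. The other misses only the week-6 site visit and drops out of the week-12 comparison as well.

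The Discussion uses biomarker changes at 6 and 12 weeks, beside self-report, to judge effectiveness. The primary outcome is self-reported by unblinded workers, dispenser records exist in the intervention arm only, and dosimeters are worn by 10 workers per group and measure external dose. The biomarkers are therefore the main objective measure of internal dose in both arms, and samples already collected should not be lost to the choice of test.

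**Working it through.** **The plan's own figure.** The Power Calculation says: "We assumed that 25% of the outdoor workers in the control groups will use sunscreen". It expects 50% in the intervention groups, with a two-sided 0.05 level and 80% power. With pooled variance and no continuity correction:

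n = [1.960 × √(2 × 0.375 × 0.625) + 0.842 × √(0.25 × 0.75 + 0.50 × 0.50)]² / 0.25² = (1.342 + 0.557)² / 0.0625 ≈ 57.7, so 58 per arm.

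The stated 58 reproduces. Recruiting 100 tolerates a loss of 1 − 58/100 = 42%. That is a margin for the primary outcome, not a forecast of loss, and no figure is given for the biomarkers.

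**Mechanism.** A standard repeated-measures ANOVA routine (AnovaRM in statsmodels), given 10 subjects at three times with one value missing, stops with an unbalanced-data error. Incomplete workers must be removed before it will run.

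**Precision at week 6.** Assumptions: all 200 workers sampled at baseline, loss spread evenly over the 12 weeks (half before week 6), equal variances, no other missed visits. With total loss d:

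- workers with a baseline and week-6 pair = 200 × (1 − d/2)
- workers with all three samples = 200 × (1 − d)
- standard error ratio = √(pairs / triplets)

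| Loss by week 12 | Pairs | Triplets | Pairs unused | SE ratio |
|---|---|---|---|---|
| 5% | 195 | 190 | 5 | 1.01 |
| 10% | 190 | 180 | 10 | 1.03 |
| 20% | 180 | 160 | 20 (11%) | 1.06 |
| 42% | 158 | 116 | 42 (27%) | 1.17 |

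Timing matters. If all loss comes before week 6, nothing is wasted and the ratio is 1.00. If all comes after, it is √(200/160) = 1.12 at 20% and √(200/116) = 1.31 at 42%. Withdrawal costs the week-12 comparison no pairs, because a worker who has left has no week-12 sample under any method.

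**Bias at week 6, if loss follows the week-6 level.** Illustrative simulation: 200 workers, true changes of 0.30 SD at week 6 and 0.50 SD at week 12, the same correlation between all visits (0.3, 0.5 or 0.7), and dropout after week 6 more likely at a higher week-6 level. Mean estimated week-6 change:

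| Loss | Complete triplets | All pairs, or mixed model |
|---|---|---|
| about 13% | 0.23 to 0.26 | 0.30 to 0.31 |
| about 24% | 0.15 to 0.23 | 0.30 to 0.32 |
| about 44% | 0.07 to 0.19 | 0.30 to 0.31 |

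The week-12 change stayed near 0.50 with triplets and with the mixed model. That result rests on the equal correlations assumed.

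**A different mechanism.** Simulation with 200 workers, correlation 0.5, the same true changes, and about 44% loss driven by each worker's stable level, half of it before week 6. Complete triplets gave 0.31 and 0.50, essentially unbiased, because a stable level cancels within a worker. A random-intercept mixed model gave about 0.25 and 0.37, too low. Week-6 contrasts on all available baseline pairs remained unbiased under this mechanism too, and were at least as precise as complete triplets.

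**The case against.** The strongest reply is that the article nowhere says a worker with a missed visit is excluded. The name of the test is loose, and comparing each later visit with baseline also fits two separate paired contrasts, which would keep the week-6 samples of later withdrawals. Handling of missing samples is commonly left to the analysis plan, and one is announced. All of this stands, and it makes the point conditional. It does not remove it: two stand-alone contrasts would ordinarily be called paired t-tests, and the analysis plan will start from the test published here.

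A reader might infer that the biomarker result will describe only workers with perfect attendance. The documents do not support that as a fact. A reader might also hold that a complete-triplet analysis is valid only if those lost are a random subset. That is wrong, as the stable-level simulation shows, and there the random-intercept model did worse. Neither method is better under every kind of loss.

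It is also fair that the cost is modest: about 6% on one standard error at 20% loss, for a secondary outcome with no stated power target.

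Finally, the planned sentence describes change from baseline and names no comparison between arms, and replacing the test does not supply one. That is a separate matter.

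**Conclusion.** The point holds in conditional form. Run as a classical repeated-measures ANOVA, the named test is a complete-case analysis, and week-6 samples from workers who later withdraw would not enter the week-6 comparison.

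Under even loss, the week-6 standard error would be about 6% larger at 20% loss and about 17% larger at 42%. Both rates are assumptions: the first is illustrative, and the second is only what the recruitment margin tolerates. If loss is unrelated to biomarker levels, the cost is precision alone. If it depends on the week-6 level, the week-6 change can be biased, by an amount the documents do not allow anyone to predict. The week-12 comparison is little affected by withdrawal; workers who miss only week 6 would be an additional loss there.

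The primary analysis is untouched. This is a worthwhile, inexpensive improvement to a secondary analysis, not a flaw that undermines the trial.

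**What to change.** In the analysis plan, before any data are seen, replace the paired ANOVA with an analysis that uses all available visits. Either of these would do:

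- a linear mixed model for repeated measures, with time as a factor, within-worker correlation, and the log scale if levels are skewed; or
- separate contrasts of week 6 and week 12 against baseline, each on every available pair.

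Keep the multiplicity correction for the two comparisons, and report the number of samples at each visit.

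The small downside is that the mixed model assumes data missing at random and can be biased if loss depends on a worker's unobserved stable level. If it is chosen, give the available-pair contrasts beside it as a check.

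The cost is a sentence or two in the analysis plan, with no extra samples, visits or assays. The article reports that recruitment had not started at submission.
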